**Substance use**		
Ever smoked?	CV	One question from substance initiation index [29]
Smoking status	CV	ASSIST study version of NatCen/NFER question [64]
Ever drunk a drink?	CV	NatCen/NFER [65]
Age of first drink?	CV	NatCen/NFER [65]
Frequency of drinking	CV	NatCen/NFER [65]
Ever little drunk?	CV	Adapted from HBSC questionnaire
Little drunk in last 3 months?	CV	Adapted from HBSC questionnaire
Ever really drunk?	CV	Adapted from HBSC questionnaire
Really drunk in last 3 months?	CV	Adapted from HBSC questionnaire
Ever taken drugs	CV	Adapted from HBSC / NatCen/NFER

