### Sample size

We will aim to recruit 378 families in each arm of the trial (756 families in total). This will provide us with at least 80% power at the 2.5% level (halved to account for our two primary outcomes) to detect either a 12% difference in young people reporting having drunk alcohol (assuming a control group prevalence of 48%
[4]), or a 10% difference in young people reporting having been drunk (assuming a prevalence of 22%
[4]), at two year follow-up. This sample size is based on an average family in the trial having 1.25 young people, an intracluster correlation coefficient (ICC) of 0.2 and is adjusted to allow for 25% loss to follow-up (including withdrawals from the trial by participants prior to 24 month follow-up).

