### Analysis

#### Main analysis

The primary analyses will be based on the intention-to-treat principle and will involve fitting two-level logistic regression models to our primary outcomes (reported drinking at two year follow-up and reported drunkenness at two-year follow-up), with responses from young people nested within families. The covariates in the models include those balanced at randomisation (type of family – general population/family with challenges, and average age of young people) and baseline levels of drinking and drunkenness (depending on the outcome). Trial area (used as a stratification variable at randomisation) will be adjusted for. For each primary outcome, a statistically significant result will be concluded if the p-value for the trial arm explanatory variable is <0.025. While our power calculation is based on the above, a combined test will be performed if both p-values lie between 0.025 and 0.05. This will take the correlation of the outcomes into account and provide an overall p-value for the two outcomes.

The primary analyses will also be repeated

• controlling for any baseline imbalances;

• without controlling for any of the above mentioned covariates;

• respecting the original ordinal scale (the primary questions are asked on an ordinal scale ranging from 0 occasions to 40+ occasions) using an ordinal regression model; and

• using a complier average causal effect (CACE) approach, to investigate the treatment effect in the treatment adherent.

Secondary analysis includes investigating the effect of the intervention on substance use (reported use of tobacco and cannabis) at two year follow-up by fitting two-level logistic regression models, controlling for baseline reports of substance use, as well as the variables balanced at randomisation (all models will control for the variables that were balanced on at randomisation). The effect of the intervention on the proportion of young people reporting alcohol-related problems will be analysed similarly. The effect of the intervention on substance initiation (alcohol, tobacco and cannabis) will be investigated by fitting two-level Cox proportional hazards models (young people nested within families) for those participants who had not already initiated at baseline.

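### The drunkenness model leaves out baseline drinking, although it is collected; putting both baseline alcohol measures in both primary models is a small, nearly free gain and protects against loss that differs by arm

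*Protocol article*

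**What the plan says.** The Main analysis section fits one two-level logistic model per primary outcome, with young people nested in families. Covariates include family type and average age from the minimisation, and "baseline levels of drinking and drunkenness (depending on the outcome"); trial area is also adjusted for. The parenthesis has a function only if the drinking model takes baseline drinking and the drunkenness model takes baseline drunkenness.

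Table 2 (Substance use, young people at baseline) collects both kinds of measure and labels all of them as covariates. On drinking it has "Ever drunk a drink", age at first drink and drinking frequency. On drunkenness it has four items: a little drunk and really drunk, each ever and recently, for example "Really drunk in last 3 months".

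The Sample size section plans for "at least 80% power at the 2.5% level (halved to account for our two primary outcomes"), and its total "is adjusted to allow for 25% loss to follow-up".

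**The concern.** Children are 10–14 at entry. Two years later the plan still assumes only 22% drunk in the last 30 days, against 48% drinking. At baseline, drunkenness is therefore likely to be the rarer of the two. A covariate that is 'no' for nearly every child separates few of them. Baseline drinking would divide that large never-drunk group, but the rule keeps it out of the drunkenness model.

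Two things are at stake for one of the two primary outcomes:

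- **Power.** A prognostic covariate already in hand is not used.
- **Loss to follow-up.** If children who drank at baseline are lost at different rates in the two arms, the followed-up groups differ in baseline drinking, and a model without it carries that difference into the arm effect. This is possible: families are told their allocation (Recruitment), one arm gets seven weekly sessions and the other a leaflet (Intervention), and the Discussion expects retention difficulties.

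**Working it through.** **1. The plan's own figure.** Inputs from Sample size: "We will aim to recruit 378 families in each arm of the trial (756 families in total"); a "12% difference in young people reporting having drunk alcohol (assuming a control group prevalence of 48"%); a "10% difference in young people reporting having been drunk (assuming a prevalence of 22"%); 1.25 young people per family; ICC 0.2; 25% loss. Sidedness is not stated; two-sided is assumed.

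- Design effect: 1 + (1.25 − 1) × 0.2 = 1.05.
- Drinking, 48% vs 36%, alpha 0.025, 80% power, continuity-corrected: 337 young people per arm.
- 337 × 1.05 = 353.9; ÷ 0.75 = 471.8; ÷ 1.25 = 377.4, rounded up to **378 families**. The stated figure reproduces.
- Drunkenness, 22% vs 12%, needs 321.4 families on the same basis, so drinking drives the size.
- Effective number per arm: 378 × 1.25 × 0.75 ÷ 1.05 = 337.5. Without continuity correction this gives about 82% power for drinking and 89% for drunkenness.

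These figures use unadjusted proportions, so the covariate choice does not affect them.

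**2. Power, random loss.** Simulation: 945 young people (756 × 1.25), 25% loss, drunkenness 22% vs 12%, 1,500 data sets, each fitted both ways. Assumed: 25–40% drinking at baseline, 15% of those having been drunk, odds ratio 3 of baseline drunkenness for later drunkenness. The efficiency ratio is the squared ratio of (mean estimate ÷ mean SE).

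| Assumed OR of baseline drinking; share drinking | Own baseline: log OR / SE, power | Both: log OR / SE, power | Efficiency ratio |
|---|---|---|---|
| 2; 40% | −0.757 / 0.2139, 0.917 | −0.768 / 0.2157, 0.924 | (3.561 ÷ 3.539)² = 1.01 |
| 3; 40% | −0.776 / 0.2158, 0.926 | −0.805 / 0.2198, 0.933 | (3.662 ÷ 3.596)² = 1.04 |
| 5; 40% | −0.779 / 0.2173, 0.931 | −0.838 / 0.2255, 0.946 | (3.716 ÷ 3.585)² = 1.07 |
| 3; 25% | −0.771 / 0.2150, 0.917 | −0.799 / 0.2193, 0.926 | (3.643 ÷ 3.586)² = 1.03 |

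The gain is 0.7–1.5 points of power. The standard error rises slightly; the gain comes from the conditional estimate moving away from zero. Power here is above 89% because family clustering was not simulated.

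A second simulation that also adjusts for age (22% vs 12%, 40% drinking, 5–20% drunk at baseline) gives about 1–8% efficiency and 0.3–2 points of power. On 337.5 effective young people per arm, that is worth 0.01 × 337.5 ≈ 3 to 0.08 × 337.5 = 27.

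**3. Loss related to baseline drinking, no true effect.** With 40% drinkers, let 40% of them be lost and 0.25 − 0.15 × 0.4 ÷ 0.6 = 15% of the others. Drinkers among those followed up: (0.4 × 0.60) ÷ 0.75 = 32%.

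- *Same pattern in both arms:* 32% vs 32%, so nothing is there to bias the comparison. Across the four settings in the table, the own-baseline model has mean log OR −0.002 to +0.012 and type I error 0.018–0.031. Simulation error at 0.025 is √(0.025 × 0.975 ÷ 1,500) = 0.004, so this is compatible with nominal.
- *Control arm only:* 32% control vs 40% intervention. Log OR +0.04 to +0.13; type I error 0.025–0.050.
- *Opposite patterns (extreme):* the intervention arm keeps (0.4 × 0.90) ÷ 0.75 = 48%, against 32%. Log OR +0.10 to +0.24; type I error 0.05–0.17.
- *Both covariates in the model, last two patterns:* mean log OR within 0.01 of zero, type I error 0.020–0.030.

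In the age-adjusted simulation, losing 30% of drinkers in control and 50% in intervention gives log OR about −0.05 to −0.09 and type I error 2.5–4.1% for the own-baseline model. With both covariates there is no bias and type I error is about 2.4%. The sign of the bias depends on which arm loses more drinkers.

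**The case against.** Adjusting each outcome for its own baseline plus the randomisation factors is ordinary practice, and almost any trial could add another prognostic covariate. The covariate list is introduced as a list of inclusions, not as exhaustive, and exact definitions may sit in the SAP, which is not shown. Baseline drunkenness is measured by four items, including the low threshold of ever having been a little drunk, so it may be less sparse than assumed; age is already in the model and carries part of the same information. Planned power for drunkenness is already about 89%. The primary analyses are also repeated with adjustment for baseline imbalances, where baseline drinking could enter.

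Most of this stands, and it is why the gain is small. It does not remove the point. The parenthesis is a stated rule about which baseline goes where. The repeat analysis is secondary and depends on an imbalance being seen; arms balanced at randomisation can still diverge among those followed up.

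A reader might infer more: that the drunkenness analysis is biased by drinking-related loss, or materially short of precision. The documents do not support either. They give one overall loss figure of 25% and nothing on loss by arm or by drinking, and loss equal across arms causes almost no bias. Nor does the absence of a missing-data method for the main analysis count, since that is commonly left to the SAP.

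**Conclusion.** The point holds as a worthwhile, low-cost improvement to a stated covariate rule, not as an error. On the natural reading, the drunkenness model omits a collected covariate that is probably more informative than the one it uses. The gain is about 1–8% in efficiency, or 0.3–2 points of power. Protection against bias matters only if drinking-related loss differs by arm: then type I error in the age-adjusted check reaches 2.5–4.1% against a nominal 2.5%, and it is higher only under more extreme patterns.

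All sizes rest on assumed baseline prevalences, associations and loss patterns. The simulations tabulated above also ignore family clustering, age and area. That baseline drinking is the better separator is a judgement from the age range and the follow-up prevalences; the documents report no baseline figures.

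**What to change.** Delete the parenthesis and state that both primary models adjust for baseline drinking and baseline drunkenness, alongside family type, average age and trial area. Name the Table 2 items used for each. Keep the collected drinking-frequency measure in the drinking model; a single three-level variable (never drank, drank but never drunk, been drunk) would coarsen the own-outcome baseline for the outcome that drives the sample size.

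The cost is a line of text and one or two extra parameters. No new data are needed and the sample size is unchanged. The odds ratios become conditional on one more covariate, so they shift slightly from those of the current models. The change should be fixed before outcome data are seen, since adding the covariate later would look data-driven. The Sub-group & interim analysis section already foresees a later SAP version before any analysis, which is a suitable place for it.

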### Randomisation

Families agreeing to participate in the research trial and who provide baseline data will be randomised using a computerised randomisation facility that will randomise families within strata defined by area (7) and use minimisation on the following variables:

• the category to which the family have been assigned (general population/family with challenges);

• age of children wishing to attend the programme (<12/12+). A mean will be taken if there is more than one child; and

• the number of children in the family wishing to attend the programme (1/>1).

There will be complete concealment of the randomisation sequence, set up securely within the randomisation database by the statistician, from the field recruitment staff and other trial team members. A random element, set at 80%, will also be used to increase the integrity and reduce the deterministic nature of the randomisation process.

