Educational achievement at 16 will be compared between trial arms by fitting a two-level logistic regression model (young people nested within families) comparing the proportion of young people who obtain five or more GCSEs at a grade C or above (GCSE Grades use an A*-G scale, with A* being the highest score). The proportion of young people who continue in education beyond 16 will be similarly compared between trial arms by fitting a logistic regression model. This analysis will be performed on the whole sample following the date that all participants (young people) should have completed school Year 11 when GCSEs are normally awarded. Other secondary and tertiary outcomes (e.g. parenting and child management, parent–child affective behaviour and wellbeing and stress) will be analysed by fitting similar regression models, controlling for clustering of responses within families (as appropriate) and controlling for variables that were balanced on at randomisation.

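### The covariate rule for the secondary and tertiary models does not clearly include trial area, and number of children is missing from the covariates listed for the primary models

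*Protocol article*

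**What the plan says.** **Randomisation.** The computerised facility will "randomise families within strata defined by area (7) and use minimisation on the following variables". Three variables follow: family category (general population or with challenges), age of the children (under 12, or 12 and over, averaged if there is more than one child), and "the number of children in the family wishing to attend the programme (1/>1").

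**Main analysis, primary models.** The covariates include "those balanced at randomisation (type of family – general population/family with challenges, and average age of young people"), plus the baseline level of the outcome. Area follows in its own sentence: "Trial area (used as a stratification variable at randomisation) will be adjusted for".

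**Main analysis, secondary models.** For tobacco and cannabis use the text adds baseline substance use and states that "all models will control for the variables that were balanced on at randomisation". Alcohol-related problems are to be handled in the same way. Substance initiation gets two-level Cox models.

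**Main analysis, education and remaining outcomes.** The passage on education reads: "Educational achievement at 16 will be compared between trial arms by fitting a two-level logistic regression model (young people nested within families"). It names no covariates of its own, so it depends on the general rule. Other secondary and tertiary outcomes get similar models, "controlling for clustering of responses within families (as appropriate) and controlling for variables that were balanced on at randomisation".

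**The concern.** The rule for every non-primary model rests on one label, the variables balanced on at randomisation. The only place that spells the label out lists two variables. Area is not one of them; it is brought in under a different description, for the primary models. Number of children is not listed either, although it is a minimisation variable. Two analysts could follow the text faithfully and fit different covariate sets.

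Allocation within area removes between-area differences from the treatment contrast. A model that ignores area leaves those differences in the error term, so its standard error overstates the sampling error of its own estimate. What is at stake is a small loss of efficiency and a mismatch between design and analysis, not bias in favour of the programme.

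Some variation between areas is plausible on the article's own account. The Intervention section says that differences in available services across areas will continue, area is a planned subgroup, and the economic evaluation separates costs and outcomes by area.

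**Working it through.** **1. The covariate sets side by side**

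| Variable | Randomisation | Named for primary models | Named for other models |
|---|---|---|---|
| Trial area | stratum | yes, separate sentence | no |
| Family category | minimisation | yes | through the label |
| Mean age | minimisation | yes | through the label |
| Number of children | minimisation | no | only if the label means the Randomisation list |

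If the label already covered area, the separate area sentence in the primary paragraph would be unnecessary. That favours the narrow reading without proving it.

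**2. Size of the sample**

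The article gives no figure for area effects. Its sample size reproduces. Detecting 48% against 36% at two-sided 2.5% (sidedness assumed) with 80% power and a continuity correction needs 337 young people per arm. With design effect 1 + (1.25 − 1) × 0.2 = 1.05, the number of families is 337 × 1.05 / 1.25 / 0.75 = 377.4, which rounds up to 378 per arm. Young people followed up: 378 × 1.25 × 0.75 = 354 per arm, or about 708 in all.

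**3. Logistic models**

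Simulation assumptions: seven equal areas, 350 young people per arm, arms balanced within area, 40,000 replicates, two-sided 5% tests, single-level models. Power is for a log odds ratio of −0.5 within area. The between-area standard deviation (SD) on the log-odds scale is assumed. Results at 48% prevalence:

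| SD between areas | Area prevalence | Model SE / true SE, area omitted (no effect) | Coverage of 95% CI, area omitted (no effect) | Power, area omitted / included | Estimand, area omitted (−0.50 if included) | CI width, omitted / included (no effect) |
|---|---|---|---|---|---|---|
| 0.2 | 41–55% | 1.01 | 94.9% | 89.7 / 89.8% | −0.495 | 0.99 |
| 0.4 | 34–63% | 1.02 | 95.1% | 88.6 / 89.3% | −0.481 | 0.98 |
| 0.6 | 27–69% | 1.04 | 95.5% | 86.4 / 88.2% | −0.460 | 0.95 |
| 0.8 | 22–75% | 1.07 | 96.1% | 82.7 / 86.1% | −0.434 | 0.93 |

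At 22% prevalence the SE ratios are 1.00, 1.02, 1.02 and 1.05. At 10% they do not exceed 1.02.

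The last column is below 1 throughout: the interval for the log odds ratio is wider with area in the model. The gain from adjustment comes from an estimate less drawn towards zero, and it shows as power. Clustering within families was not simulated; with a design effect of 1.05 it should change little.

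**4. Linear models**

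If area explains a share s of the variance, the interval without area is wider by the factor 1/√(1 − s). For s = 1, 2, 5 and 10% this is 0.5, 1.0, 2.6 and 5.4%. At s = 5%:

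- type I error = 2[1 − Φ(1.96/√0.95)] = 2[1 − Φ(2.011)] = 4.4%
- nominal 80% power becomes Φ(2.80 − 2.011) = 78.5%

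**5. Sparse outcomes**

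The Background gives 6% past-week smoking among 11–15 year olds in England. Applied here as an assumption, 708 × 0.06 ≈ 42 events, or about 6 per area and 3 per area per arm. Area effects would be thinly supported for such an outcome.

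**The case against.** The strongest reply is that the omission is inferred. No sentence excludes area from any model, and randomising within areas is itself a way of balancing on area, so the general rule can be read to include it. The two-variable list cannot define the label strictly, because it also drops number of children and is introduced as a partial list. Covariate lists for individual secondary models commonly sit in the statistical analysis plan, which the article mentions and which is not shown.

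Most of this stands, and it limits the point. A reader might infer that the plan states area will be left out; it does not. What remains is that the article is not silent. It sets a rule for all models, using a label that its own list fills incompletely.

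A reader might also infer that the secondary confidence intervals are too wide across the board. That does not hold. In logistic models an interval without area is wide only relative to that estimate's own sampling error, and adding area widens the log-odds interval slightly. The expectation of narrower intervals fits linear models only.

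The reply is also right that the effect is small and errs on the cautious side, that its size rests on assumed variation, and that it concerns outcomes for which the article makes no power claim.

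**Conclusion.** The point holds as a minor defect of specification. On the better reading, though not the only one, area is not carried into the secondary, education and tertiary models. Number of children is missing from the covariates stated for the primary models, whichever way the label is read.

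If area is omitted, logistic-model standard errors are about 0–2% too large for a between-area log-odds SD up to 0.4, and up to about 7% too large at 0.8. The power cost at 48% prevalence runs from 0.1 points at SD 0.2 to 3.4 points at SD 0.8. Linear-model intervals are 0.5–5.4% wider if area explains 1–10% of the variance. These figures assume equal areas and a between-area variation that the article does not report. The effect of leaving out number of children was not quantified.

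Nothing here suggests inflated type I error from omitting area, and the primary analyses do adjust for it.

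**What to change.** In Main analysis, replace the general rule and the matching phrase for other secondary and tertiary outcomes with one statement, and bring the primary covariate list into line with it:

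> All primary, secondary and tertiary models will adjust for trial area and for the three minimisation variables: family category, mean age of the children attending and number of children attending.

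Enter area as fixed effects in the regression models and as strata in the Cox models. For rare outcomes such as weekly smoking, check event counts by area before fitting and say in advance what will be done if they are too small. If the statistical analysis plan already says this, the article's wording only needs to match it.

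The cost is wording, six parameters per regression model for area and one for number of children. Both are known for every family at randomisation.

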#### Sub-group & interim analysis

There is no planned interim analysis. Exploratory sub-group analyses are planned for:

• age of young person at baseline;

• gender of young person;

• smoking behaviour of young person at baseline;

• parental drinking behaviour at baseline;

• socio-economic status (using both the Family Affluence Scale and occupational status, which will be analysed separately);

• family status (general population/with challenges); and

• trial area.

Up to two subgroup analyses will be performed to test hypotheses generated from the process evaluation. These will be specified in a later version of the Statistical Analysis Plan (SAP) before any trial analysis takes place, and will be generated by researchers with no access to the trial outcome data. Subgroup analyses will also be performed to assess differential treatment effects for those who may be at high risk of substance initiation and misuse (based on baseline scores for SDQ, the Family Relationship Index and the General Child Management Scale).

